### Objectives

The primary objective of this study is to estimate the FPR of patients with resectable non-metastatic high-grade STS treated with MRI habitat–directed neoadjuvant GARD-optimized RT dose. Secondary objectives are related to the safety and clinical outcomes associated with radiomic habitat-directed radiation dose escalation. Exploratory objectives are concerned with the identification of radiomic biomarkers that correlate with pathologic response that in turn could be used to inform biologic plan adaptation in the future. Biopsy of each habitat will be stored for future genetic testing and correlation with liquid biopsy samples taken at the time of each multiparametric MRI (mpMRI).

#### Primary endpoint

The rate of FPR (tumor response ≥ 95%) at the time of surgery.

#### Secondary endpoints

Margin status estimate as defined as the final tumor margin of the surgical specimen will be conducted by pathologist. A clear margin (R0) or a positive margin (R1/R2) will be designated, along with the location of the margin, which will be radiographically correlated to the habitat.Pathologic response of each habitat delineated on pathology specimen as determined by the difference in tumor response by various heterogenous portions of the tumor, as delineated by MRI-directed pre-RT clip placement.Rate and types of adverse events evaluated during weekly on-treatment visits (OTVs) up to 4 months (< 120 days) post-surgery.Disease control, determined as the absence of local tumor progression, to be per assessment of the treating radiation oncologist (i.e., clinical assessment) and radiologist (i.e., radiological assessment) for up to 4 months after surgery.Survival, as assessed by clinical visit, virtual visit, or telephone visit for up to 4 months after surgery.

#### Exploratory endpoints

Prediction of tumor response with an early mid-treatment mpMRI at weeks 2 to 3.Collection of tissue habitats for future genomic-radiomic correlations and response to radiation.Collection of liquid biopsies for correlative studies regarding response to radiation.Correlation of diagnostic mpMRI and 0.35 T MRL sequences.

#### GARD modeling of STS

In previous studies we generated the distribution of GARD for 231 STS patients, assuming standard of care neoadjuvant RT dose (50 Gy in 25 fractions), and an average beta of 0.045 [11, 38, 39]. As shown in Fig. 2, GARD ranged from 22.96 to 31.37, with a higher GARD predicting a higher probability of tumor response. In addition, since the GARD calculation is based on the linear-quadratic model, the distribution curve (Fig. 2) has a linear region where there is a rapid increase in GARD. We modeled two possible scenarios. In the first scenario, we assumed that the baseline response to neoadjuvant RT (based on SOC dose) is ∼ 8% (7.9%), as demonstrated in the recent phase 2/3 clinical trial [6]. In a second scenario, a review of our center’s experience revealed that 37 of 202 (18.3%) STS patients treated with standard neoadjuvant RT alone experienced an FPR. Next, we identified approximately the top 8th and 18th percentile values in the GARD distribution (31.37 and 22.96), the highest 8% and 18% radiosensitive sarcomas are most likely to achieve a FPR, which we hypothesize are the GARD target values that optimize clinical outcome. It should be noted that the hypothesized GARD targets are both located after the linear region of GARD suggesting that uniform increase in dose are likely to impact the outcome of these patients. We next modeled the impact on GARD distribution if the dose was 60 and 70 Gy. As shown in Fig. 2, the number of patients that are predicted to achieve each GARD target (31.37 and 22.96) would increase with homogenous dose to 60 Gy (15.2–26.8%) and 70 Gy (26.8–60.2%), depending on true baseline response rate.

**Fig. 2 Fig2:**
[figure not shown]
Distribution curve of the cumulative incidence of GARD from 231 STS samples. GARD pathologic response prediction based on historic (8%) and institutional (18%) FPR rates to standard neoadjuvant radiotherapy (50 Gy in 25 fractions), with GARD thresholds of 31.37 and 22.96, respectively. Note the effect that dose escalation with 60 Gy (red) and 70 Gy (green) in 25 fractions has on the percent of patients that are predicted beyond the thresholds. Since both GARD targets are after the linear region in the curve, a uniform dose increase quickly impacts the number of patients that achieve each of the GARD target values. Since habitats are dichotomized based on the gross tumor volumes median value, then 50% of the volume will receive standard dose and the other half will receive dose escalation of either 60 or 70 Gy. Therefore, the probability of achieving a FPR is 8 to 18% for the standard half and an average of 15.2–60.2% to the escalated half of the GTV, would predict for a > 24.3% estimated FPR for the cohort. A tripled FPR rate (8–24%) is a modest estimate that assumes complete dose conformality, with neighboring habitats adjacent to one another, this would be a conservative minimum FPR increase we expect to see clinically. The estimated FPR is assuming the same probability of response for each habitat, but knowing that radioresistant hypoxic regions often require > 30% higher dose for response [40], the radiomic habitat directed approach may better identify the regions that would most benefit from dose escalation, therefore improving overall response

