**Fig. 6 Fig6:**
[figure not shown]
Specimen radiograph displaying markers for each habitat and to help orient with preoperative imaging (**A**). At time of pathological evaluation, the specimen is mapped to a grid to determine percentage of pathological response throughout the specimen (**B**)

The pathologists on this study are sarcoma specialized, and cross-review is performed on all cases by a fellow sarcoma specialized pathologist. No molecular markers or assays are required to assess pathologic response, as it is a microscope-based assessment. To help the pathologist ascertain which part of the tumor they are analyzing, the 3 habitats biopsied before the start of RT will be designated with specialized clips in each location (minimum of 1.5-3 cm apart) (Fig. 7). A radiograph is completed on the resected pathologic specimen, to orient the pathologist and determine the habitat locations for intratumoral response analysis. The entire tumor is analyzed for pathologic response along with each habitat marked with clips. The pathologists also mark off the sections that had viable cells remaining (Fig. 6), so future radiomic-dose correlations can be determined, which will account for cumulative dose and spillover.

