### Statistical considerations

#### Sample size and interim analyses

The primary endpoint is evaluating the FPR rate of patients with resectable non-metastatic high-grade STS treated to GARD-optimized RT dose utilizing MRI habitat–directed neoadjuvant radiation therapy. GARD-based modeling predicted that increasing the dose (60 to 70 Gy) would triple the FPR to an average of > 24.3%. The null hypothesis that the true FPR is 7.9%, which will be tested against a 1-sided alternative hypothesis that the FPR is 24%. We determined the sample size of a maximum of 43 patients using Fleming’s three-stage optimal design, which has a one-sided significance level of 5% and a power of 81.8% if the true FPR is 24% under the alternative hypothesis. The trial is carried out in 3 stages. In the first stage, a total of 13 evaluable patients will be accrued. If there are at least five FPRs among these 13 patients, the study will be considered a success, but will continue to accrue to 23 total patients to obtain further sufficient information about primary and secondary endpoints. Otherwise, it will move onto the second stage that will accrue an additional 10 evaluable patients. If there are two or fewer FPRs in the total of 23 subjects in the second stage, the trial will be stopped for futility. If there are ≥ 5 FPRs among these 23 patients, the study will be considered a success and accrual would end after the 23 total patients. Otherwise, ten additional evaluable patients will be accrued in the final third stage, resulting in a total sample size of 36. The null hypothesis will be rejected if there are ≥ 7 FPRs among these 36 subjects. Considering a dropout rate of 15%, approximately 43 subjects will be enrolled. If the true response rate is 7.9%, then the probability of stopping early for futility is 71.4%, the probability of stopping early for success is 4.4%, and the expected sample size is 26.2. When the trial is considered successful at the first or second interim analysis, a total of 23 evaluable patients will be accrued.

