Overall, the HEAT trial takes full advantage of current understanding within various fields (i.e., radiomics, genomics, and MRI-guided RT) to push beyond traditional one-size-fits-all RT paradigms. It represents an important step towards biologically and radiographically guided adaptive radiation therapy. If successful, the HEAT trial would provide the first evidence that GARD-based dose adjustments can improve the clinical outcome of patients as predicted, improve our understanding between the relationship between radiomics and genomics, and would open a new era in radiation oncology leading to genomic and radiomic-based clinical trials and practice. In addition, the insights gathered may also enable the identification of novel radiomic and genomic biomarkers that may lead to a refinement of current personalized strategies for STS patients.

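### The predicted FPR of more than 24.3% appears to be a volume average of per-half probabilities, pooled over two baselines; it is not the probability of the whole-tumour endpoint.

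*Protocol article*

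**What the plan says.** The section on GARD modeling of STS uses two baselines for FPR at 50 Gy. One is about 8% (7.9%), from a published trial. The other is institutional: "37 of 202 (18.3%) STS patients treated with standard neoadjuvant RT alone experienced an FPR". For each baseline it reports the share of patients predicted to reach the GARD target if the whole tumour received 60 Gy (15.2% or 26.8%) or 70 Gy (26.8% or 60.2%).

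The Fig. 2 legend then takes half the tumour at standard dose and half escalated, and states "Therefore, the probability of achieving a FPR is 8 to 18% for the standard half and an average of 15.2–60.2% to the escalated half". It concludes that cohort FPR would exceed 24.3% and describes the tripling from 8% to 24% as a conservative minimum. It adds: "The estimated FPR is assuming the same probability of response for each habitat".

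Sample size and interim analyses repeats the result: "GARD-based modeling predicted that increasing the dose (60 to 70 Gy) would triple the FPR to an average of > 24.3" percent. The benchmark there is "The null hypothesis that the true FPR is 7.9" percent, and the design is one "which has a one-sided significance level of 5% and a power of 81.8% if the true FPR is 24" percent. The Discussion repeats the 24.3% and says that success "would provide the first evidence that GARD-based dose adjustments can improve the clinical outcome of patients as predicted".

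The endpoint is defined on the surgical specimen (Study design; Primary endpoint). Radiological and pathological treatment evaluation confirms this: "The entire tumor is analyzed for pathologic response along with each habitat marked with clips".

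**The concern.** FPR is a yes/no result for one whole tumour. The legend assigns an FPR probability to each half and combines the two into a cohort FPR, which the sample size section calls an average. Averaging by volume would suit a mean percentage response. It does not suit the probability that a whole specimen passes a 95% threshold, since both halves contribute viable cells to the same specimen.

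The ranges also run across two baselines. The upper figures (18% and 60.2%) belong to the institutional baseline, while the hypothesis test and the tripling claim use the 7.9% baseline.

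At stake are the justification of the 24% alternative, and so the meaning of the stated power, and the claim that a positive trial shows benefit of the size that GARD predicted.

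**Working it through.** **1. The design figure reproduces.** Inputs, from Study design and Sample size and interim analyses: stages of 13, 10 and 13 evaluable patients; success at 5 or more of 13, 5 or more of 23, or 7 or more of 36; futility at 2 or fewer of 23. The sample size text gives ten patients for stage 3, but the total of 36 and the Study design section require 13, which is used here. Five responders at stage 1 already imply five at 23, so

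P(success) = P(X23 ≥ 5) + P(X23 = 3)·P(X13 ≥ 4) + P(X23 = 4)·P(X13 ≥ 3).

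- At 24%: 0.678 + 0.101 × 0.382 + 0.160 × 0.636 = 0.819 (stated: 81.8%).
- At 7.9%: 0.031 + 0.008 = 0.039, within the one-sided 5%.

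**2. Where 24.3% could come from.** The article does not print the arithmetic. Averages that pool the baselines come near it:

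- midpoints of the two printed ranges: (13 + 37.7)/2 = 25.4%
- mean of the four escalated values, 32.25%: (13 + 32.25)/2 = 22.6%

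No variant tried gives exactly 24.3%, so averaging is an inference from the legend, from the word average in the sample size section, and from these near matches.

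**3. Averaging with the baselines kept apart** (60 and 70 Gy weighted equally in the escalated half):

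| Baseline | Escalated half | Average of halves | Ratio to baseline |
|---|---|---|---|
| 8% | (15.2 + 26.8)/2 = 21.0% | (8 + 21.0)/2 = 14.5% | 1.8 |
| 18% | (26.8 + 60.2)/2 = 43.5% | (18 + 43.5)/2 = 30.75% | 1.7 |

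The weights do not rescue the 8% case. With the escalated half all at 60 Gy the average is (8 + 15.2)/2 = 11.6%; all at 70 Gy it is (8 + 26.8)/2 = 17.4%. To average 24.3% from 8%, the escalated half would need 2 × 24.3 − 8 = 40.6%, above the 26.8% modelled for 70 Gy at that baseline.

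**4. What the endpoint requires.** With equal halves, the viable fraction of the whole tumour is (standard half + escalated half)/2, and it must be at most 5%. If the escalated half is fully cleared, the standard half may hold at most 10%. So P(FPR) cannot exceed P(standard half responds by at least 90%). The article gives no figure for that probability.

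**5. Illustration only.** Assume that every habitat must reach its GARD target, and that each tumour has one GARD value, which rises with dose. The lowest dose that matters then sets the prediction: about 8% if habitat 3 (50 Gy) counts, or 15.2% if habitat 3 is taken as non-viable and habitat 2 (60 Gy) is limiting. These are not bounds.

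**6. Success probability of the stated rule:**

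| True FPR | P(success) |
|---|---|
| 7.9% | 3.9% |
| 14.5% | 31.6% |
| 15.2% | 35.8% |
| 24% | 81.9% |

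**The case against.** A reader might infer that the plan's own model caps FPR at the 8% baseline, or at 15.2% with habitat 3 set aside, so that the regimen is predicted to bring little or no gain. The documents do not support this, for four reasons.

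- The arithmetic in step 4 allows a gain. A tumour with 9% viable cells throughout fails; with 9% in the standard half and none in the other it holds 4.5% and passes.
- Habitat 3 is described as necrosis and fluid with low cellularity, and necrosis counts as response, so the standard-dose half may do better than 8% to 18%.
- The GARD targets are hypothesised, with higher GARD raising the probability of response. They are not a deterministic rule, and the Background says radiosensitivity varies within tumours.
- The legend bases its conservative label on assuming complete dose conformality between adjacent habitats, which leaves out dose spillover.

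These points stand and rule out any firm replacement figure. They do not validate the averaging. The printed calculation gives the standard half 8% to 18% and assumes equal response probability per habitat, so neither low cellularity nor spillover enters it. The 60 and 70 Gy figures come from homogeneous dose to the whole tumour. The target-definition section also crops the escalated volumes near normal structures and removes small regions, so the escalated share can fall below half, which works against calling 24% a minimum.

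Two further inferences also fail. Success at 5/23 (21.7%) or 7/36 (19.4%) lies below 3 × 7.9% = 23.7%, but a rejection threshold below the alternative is normal and is no defect. And the Discussion claims first evidence, not proof.

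**Conclusion.** The concern holds as a fault in the stated prediction and in the conclusion drawn from it. The figure of more than 24.3% is not shown to be the probability of the trial's endpoint. Taken at face value as an average, it depends on mixing two baselines: at the 8% baseline that is tested, averaging gives about 14.5% (11.6% to 17.4% depending on how the escalated half is split). If the true FPR were 14.5%, the trial would succeed with probability about 32% rather than 82%.

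This rests on the averaging being correctly inferred, on equal halves, and, for 14.5%, on equal weight for the two escalated doses. The 8% to 15% illustration needs the stronger assumptions given with it.

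The test against 7.9%, its type I error (3.9%), the boundaries, enrolment and the power at 24% are sound in this respect. A true FPR of 24% is not excluded; the model as printed does not establish it.

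**What to change.** - **Fig. 2 legend, Sample size and interim analyses, and Discussion:** show the derivation separately for each baseline, and state that a volume average of response probabilities is not whole-tumour FPR. Give a whole-tumour calculation with its assumptions and range, with and without habitat 3 counted as non-viable. Delete the description of the tripling as a conservative minimum. Align the matching sentences in the Abstract and Background.
- **Sample size and interim analyses:** say that 24% is the alternative used for power, and that the model does not establish it as a GARD prediction of the endpoint.
- **Aims and closing Discussion:** frame the conclusion as whether FPR exceeds the 7.9% benchmark, not as confirmation of the GARD prediction.

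The cost is text and one recalculation. The existing 231-patient GARD distribution is per patient and cannot supply habitat-level probabilities, so these must enter as stated assumptions with a range. The published prediction will probably look less favourable. Decision boundaries and enrolment stay as they are.

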**Fig. 1 Fig1:**
[figure not shown]
Trial schema. Radiation therapy begins between visit 1 and visit 2. All patients will be seen during weekly treatment visits throughout radiation therapy. Radiation therapy ends between visit 2 and visit 3. Surgical resection occurs between visit 3 and visit 4

We hypothesize that GARD-optimized RT dose for STS (60 to 70 Gy in 25 fractions), delivered to MRI defined radiomic habitats will triple the FPR rate as defined by response in the surgical specimen of ≥ 95% cellular response. With 36 evaluable patients, this study has 81.8% power to detect an increase in the FPR rate from 7.9% (benchmark selected based on historical data) to 24%, with a one-sided alpha = 0.05. A Z-test with continuity correction will be used to determine changes in the FPR. Assuming 15% of patients will be unevaluable, up to 43 patients will be enrolled within 24 months. This trial uses Fleming’s 3-stage design, in which stage 1 accrual is 13 evaluable patients over 6 months, with a projected accrual rate of 2 patients per month. Stage 2 accrual is 10 and the final stage accrual is 13. Assuming 50% of the eligible patients over a 12-month period enroll in this trial, 3 patients per month will enroll.

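### The 24% alternative pools two baseline scenarios but is tested against the 7.9% null of one; matched to that null, the plan's own model gives 11.6–17.4%

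*Protocol article*

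**What the plan says.** The section GARD modeling of STS sets up two scenarios. In the first, standard 50 Gy gives an FPR of 7.9% (GARD target 31.37). In the second, it gives 18.3%, from 37 of 202 patients at the centre (target 22.96). The share of patients predicted to reach the target "would increase with homogenous dose to 60 Gy (15.2–26.8%) and 70 Gy (26.8–60.2%), depending on true baseline response rate". The lower figure of each pair therefore belongs to the 8% baseline and the upper figure to the 18% baseline.

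The Fig. 2 legend assigns half the tumour volume to standard dose and half to 60 or 70 Gy. It takes "8 to 18% for the standard half and an average of 15.2–60.2% to the escalated half of the GTV", arrives at more than 24.3% for the cohort, and describes a tripling from 8% to 24% as modest and as a conservative minimum.

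Sample size and interim analyses says the modelling "would triple the FPR to an average of" more than 24.3%, and sets the test as follows: "The null hypothesis that the true FPR is 7.9%, which will be tested against a 1-sided alternative hypothesis that the FPR is 24" per cent. The design is given a "one-sided significance level of 5% and a power of 81.8% if the true FPR is 24" per cent. Aims, Study design and Discussion repeat the contrast of 7.9% with 24% (24.3% in the Discussion).

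**The concern.** The two ranges in the legend run from the lowest value of one scenario to the highest value of the other. An average drawn from both describes neither baseline. If 7.9% is the true standard rate, the values from the 18% scenario do not apply. If they do apply, the comparator is 18.3%, not 7.9%.

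The article presents 24% as what the model predicts, and the Discussion treats success as evidence that GARD-based dosing works as predicted. The distance between the null and the model-based prediction therefore determines what either result can say about the model. If the prediction at a 7.9% baseline is well below 24%, the printed power does not describe the chance of confirming it.

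**Working it through.** **1. Reproducing the stated power.** Inputs: null 7.9%, alternative 24%. Stage sizes are 13, 10 and 13 (Study design: "Stage 2 accrual is 10 and the final stage accrual is 13"). Boundaries are in Sample size and interim analyses: early success ("If there are at least five FPRs among these 13 patients"); futility ("If there are two or fewer FPRs in the total of 23 subjects in the second stage"); success at 5 or more of 23; rejection at 7 or more of 36. That section speaks of ten patients in the last stage but totals 36, and 36 − 23 = 13. Using 10 gives 77.0% power, so I used 13.

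With X_n the number of FPRs in the first n evaluable patients, the exact binomial probability of success is

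P(X_13 ≥ 5) + P(X_13 ≤ 4, X_23 ≥ 5) + P(X_13 ≤ 4, 3 ≤ X_23 ≤ 4, X_36 ≥ 7).

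- At 24%: 0.182 + 0.497 + 0.140 = 81.9%, which agrees with the stated 81.8%.
- At 7.9%: 3.9%, within the 5% level.

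**2. Prediction within each scenario.** I used the legend's average, (standard half + escalated half)/2, with the printed values. The 60:70 Gy split of the escalated half is not stated, so both extremes are shown. Equal weights are my assumption.

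| Escalated half | 8% baseline | 18% baseline |
|---|---|---|
| All 60 Gy | (8 + 15.2)/2 = 11.6% | (18 + 26.8)/2 = 22.4% |
| Equal weights | (8 + 21.0)/2 = 14.5% | (18 + 43.5)/2 = 30.75% |
| All 70 Gy | (8 + 26.8)/2 = 17.4% | (18 + 60.2)/2 = 39.1% |

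Equal-weight escalated values: (15.2 + 26.8)/2 = 21.0 and (26.8 + 60.2)/2 = 43.5.

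Largest rises: 17.4/8 = 2.2-fold and 39.1/18 = 2.2-fold. With equal weights: 14.5/8 = 1.8-fold and 30.75/18 = 1.7-fold. To reach 24% from an 8% standard half, the escalated half would need 2 × 24 − 8 = 40%. The highest value printed for that scenario is 26.8%.

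**3. What pooling gives.** With equal weights everywhere: (14.5 + 30.75)/2 = 22.6%. With the midpoints of the two ranges in the legend: (13 + 37.7)/2 = 25.35%. With a 35:65 split between 60 and 70 Gy: (13 + 0.35 × 21.0 + 0.65 × 43.5)/2 = 24.3%. The article does not show its derivation, but values near 24.3% arise from the printed figures only when the 18% scenario contributes.

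**4. Probability of success under the same rule, against the 7.9% null.**

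| True FPR | Meaning | Probability of success |
|---|---|---|
| 11.6% | 8% baseline, all 60 Gy | 16.1% |
| 14.5% | 8% baseline, equal weights | 31.6% |
| 17.4% | 8% baseline, all 70 Gy | 49.3% |
| 18.3% | centre's own rate, no benefit from escalation | 54.7% |
| 22.4% | 18% baseline, all 60 Gy | 75.7% |
| 24% | stated alternative | 81.9% |
| 30.75% | 18% baseline, equal weights | 96.0% |

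**The case against.** **The power statement is conditional, and correct.** A reader might infer that 81.8% is a calculation error. It is not: the article gives it only for a true FPR of 24%, and the exact value agrees. Alpha and boundaries are untouched. A sponsor may also choose a target effect freely. All of this stands and confines the fault to the stated origin of 24%.

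**The second scenario cannot be set aside.** This is a single-centre trial and 18.3% is that centre's own rate. Under that scenario, power is about 96% at 30.75%. This stands, so it would be wrong to say flatly that the trial is underpowered. But the same scenario implies about a 55% chance of success if escalation adds nothing, so it does not support the contrast with 7.9% either.

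**A misprint might explain 24.3%.** The value 26.8% appears twice, and one might infer that one entry should be about 40.2%. The documents do not support this as the only explanation: the 35:65 split in step 3 gives 24.3% from the printed values, and 40.2% in either cell restores the equal-weight average equally well. If the 70 Gy value for the 8% baseline were 40.2%, that scenario would give (8 + 27.7)/2 = 17.85% with equal weights, and (8 + 40.2)/2 = 24.1% only with the whole escalated half at 70 Gy. Fig. 2 was not available to settle the values.

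**The standard-dose half may matter less than the average implies.** It is tempting to argue that an overall response of 95% requires the 50 Gy half to respond by at least 90% from treatment. The article does not support that: habitat 3 is described as necrosis and fluid with low cellularity, and necrosis counts as response. Taken further, if the outcome turned on the escalated half alone, the 8% scenario would span 15.2% to 26.8%, which includes 24%; power at its 21% midpoint is about 69%. This is a fair alternative model, but not the one in the legend. Even on it, 24% lies near the top of the range and is not a minimum. The legend's remark that habitat targeting may do better carries no figure.

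**Conclusion.** The point holds as a fault in the derivation of the alternative. An FPR above 24.3%, and a tripling from 7.9%, do not follow from the article's model at the baseline being tested. On the printed values and the legend's half-and-half average, that baseline gives 11.6% to 17.4%, with power of 16% to 49% (about 32% at 14.5%, if 60 and 70 Gy are weighted equally). The main conclusion does not need that weighting: no split of the escalated half brings the 8% scenario to 24% or either scenario to a 3-fold rise. It does depend on the printed percentages being right.

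The consequence is for interpretation. If both the model and the 7.9% baseline are true, a negative result is at least as likely as a positive one and would say little against GARD. If the 18.3% baseline is true, a positive result would say little for it. The article does not itself state how a negative result would be read.

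**What to change.** - Give the predicted FPR separately for each baseline, with the range over the 60:70 Gy split, and state the split assumed for any single figure.
- Show how 24.3% was obtained, and confirm the two 26.8% entries.
- Remove the description of tripling as a conservative minimum and the statements that GARD modelling predicts tripling from 7.9%. Describe 24% as a chosen target effect.
- Beside 81.8%, print the probability of success at the scenario-matched values (16–49% for the 8% baseline, about 96% at 30.75% for the 18% baseline), and the 55% at 18.3% with no benefit from escalation.

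The cost is wording and one small table, and a less favourable power figure in print. Sample size, stage boundaries and the analysis stay as they are.
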